### Data management and analysis

#### Blinding

Due to the nature of the intervention, participants are not blinded to their study allocation. Some data collection is, however, blinded to the intervention allocation status of participants as described in the data collection section. Project managers are not blinded to the allocation status of the study participants; however, the Principal Investigators and analysts will remain blinded. Data will be analysed blinded to the intervention status of participants.

#### Interim analysis and monitoring by the Data Management Committee (DMC)

We do not expect any adverse effects of the intervention but plan to carry out two interim analyses in 2018 and 2019, which will be reported to an independent Data Management Committee (DMC) to be convened according to the DAMOCLES charter [44]. For these meetings, the DMC will be provided with a report on the two key safety measures for the trial, presented separately by trial arm. The two key safety measures are infant and maternal mortality. The DMC will decide at each meeting whether to request further analyses, which may include analysis of the study primary outcomes, and will on each occasion recommend the study should either continue or stop. The DMC may also comment on whether any changes to the trial should be made, for example if the basis of the sample size calculation is contradicted by the accumulating data or if changes are required to improve recruitment or data capture. Only the trial statistician and the DMC will be aware of the outcomes on these safety measures.

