## Methods

### Study setting

The study is conducted in Siaya County, Kenya, located on the shores of Lake Victoria, in the West of the country. Siaya County has a population of 984,069 people and is made up of six sub-counties, which are mostly rural and perform poorly on several development and health indicators [21]. As a whole, the County has a human development index (HDI) score of 0.46, significantly below the national average of 0.56 [22]. It has the highest national rates of HIV infection, TB and malaria in Kenya, and among the worst indicators of child and overall health status [23]. Infant mortality stands at 111 per 1000 live births against 49/1000 for the country, and maternal mortality at 695 per 100,000 live births against 488/100,000 in Kenya. On a few indicators, the County performs better than the national average. For instance, 38% of the population in Siaya live below the poverty line, while the country’s average is 45% [24]. The rate of immunization in children under 1 year is 72.5% against 67.5% for the country, and the rate of delivery by a skilled attendant is 69.6% against a 61.2% national average [23].

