### Data collection methods

Data are collected in person by nurses at enrolment, over the telephone by trained interviewers at key time points, and through manual extraction of routine health records supplemented by the electronic contact card system. Data are also collected to facilitate rigorous process and economic evaluations. Table 1 summarizes the data collected using each method.

**Table 1 Tab1:** Primary and secondary outcomes of the trial and sources of these data for different outcomes

Primary outcomes	Source of data
• Proportion of all eligible ANC visits made after recruitment • Delivery at a health facility • The proportion of health appointments honoured for PNC at week 2 to 6 after delivery, and months 4–12 after delivery • Proportion of referrals for ANC, PNC and child immunization attended Proportions of immunization appointments attended by children	• Abstracted health records from the health facility • Electronic system used to enrol participants into the study • Telephone surveys will collect visits made outside the study area by all “high risk” women and 50% of other women
Secondary outcomes	Source of data
• Proportion of women retained in the continuum of MNCH from pregnancy to 12 months post-delivery	• Clinic records • Electronic card system • Telephone survey 3 at 6 months after delivery
• Likelihood of a live birth and child survival 48 h after birth	• Clinic records • Telephone survey 2 at 2 weeks after EDD, if not delivered at the facility
• Likelihood of a maternal death during delivery and 48 h postpartum	• Clinic records • Telephone survey 2, 2 weeks after EDD, if not delivered at the facility
• Self-rated health of mothers, 6 months and 12 months after delivery	• Telephone surveys 1, 3 and 4 at 6 months and 12 months after delivery
• Mother’s perception of infant’s health, 6 months and 12 months after delivery	• Telephone surveys 2, 3 and 4 at 6 months and 12 months after delivery
• Proportion of mothers exclusively breastfeeding to 6 months of age	• Telephone surveys 2 and 3 and 4 at 6 months and 12 months after delivery
• Proportion of women using family planning and contraceptive use after delivery	• Telephone surveys #3 and #4 at 6 months and 12 months after delivery
• Screening and control of infections for mothers and fetus/baby during pregnancy and postnatal periods	• Clinic records (ANC, HF deliveries and PNC clinic records) • Manual collection of health records

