#### Telephone surveys

Data are collected on secondary outcomes, socio-economic characteristics, care seeking and decision-making regarding the cash transfer, using the four follow-up telephone surveys described subsequently. Some data on the primary outcomes are also collected (see Table 1). The surveys are administered to all participants in both the intervention and control groups.

Telephone survey one: after enrolment

The first telephone interview is conducted with all participants as soon as possible after enrolment. This structured questionnaire collects data on socio-economic status, self-rated health and decision-making. Information on the recent health visit is also collected, including cost and time taken to travel to the facility, waiting time, cost of all care received and satisfaction with the care received. The same questionnaire is administered to the intervention and control groups, and the interviewer is blinded to the allocation of the participant.

Telephone survey two: 2 weeks after the EDD, if no facility delivery

A phone survey is conducted with all mothers who delivered babies at home, 2 weeks after their EDD. This survey collects information on delivery date, delivery outcome, who conducted the delivery, self-rated wellness for mother and child and breastfeeding initiation. The interviewer is blind to participant allocation.

Telephone survey three: 6 months after the EDD/child birth

A telephone survey is administered to 50% of participants 6 months after the EDD, to collect data on secondary outcomes such as maternal and child deaths, self-rated health of mothers and infants, exclusive breastfeeding and utilization of family planning methods. This survey also collects information on the last health care visit including the cost of seeking care, purpose of visit, waiting time and visit experience.

A second part of the survey is used to elicit information on the receipt of any conditional or unconditional cash transfer, receipt of *Afya* transfers (in the intervention arm only), how any money received was spent and who decided how the money was spent. The interviewer is not blind to participant allocation, as some questions are related to receipt and utilization of the cash transfers.

Telephone survey four: 12 months after the actual delivery date

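### The standing DMC report lists infant and maternal mortality only, so an excess of stillbirths among women exposed since their first antenatal visit would not show unless the committee asked for it

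*Protocol article*

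**What the plan says.** The protocol article plans two interim looks ("plan to carry out two interim analyses in 2018 and 2019") for an independent committee. For its meetings "the DMC will be provided with a report on the two key safety measures for the trial, presented separately by trial arm", and "The two key safety measures are infant and maternal mortality". The committee "will on each occasion recommend the study should either continue or stop". It may also ask for more: "The DMC will decide at each meeting whether to request further analyses, which may include analysis of the study primary outcomes".

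That section does not define infant mortality. The only other use of the term with a figure is under Study setting: "Infant mortality stands at 111 per 1000 live births against 49/1000 for the country".

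The secondary outcomes include "Likelihood of a live birth and child survival 48 h after birth". Table 1 gives the sources as clinic records, plus telephone survey two for women who did not deliver at the facility. On survey two, the Telephone surveys section says: "This survey collects information on delivery date, delivery outcome, who conducted the delivery". By contrast, surveys three and four, which record later child deaths, go to half of the participants.

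**The concern.** Exposure begins in pregnancy. Women join at the first antenatal visit, and the intervention arm is paid for antenatal visits and for delivery in a facility. A stillbirth after enrolment is a death within the exposed period, yet neither named safety measure counts it.

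Infant mortality per live birth is conditional on an event after randomisation that the protocol itself treats as open to change, because it lists live birth as an outcome. Two things follow:

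- If the intervention raised stillbirths, infant mortality would not move.
- If some stillbirths became live births followed by early death, infant mortality would rise with no extra death. The reverse shift would make it fall.

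At stake is the routine information behind each continue-or-stop recommendation. It matters most at the 2018 look. Thirty of the 48 facilities began enrolling only in November 2017, and recruitment ended on 31 July 2018, so few infants could have completed a year of follow-up. Birth outcomes and early deaths would be most of the safety information then available.

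**Working it through.** The article gives no rate, boundary or power for the safety measures, so there is no figure of its own to reproduce on this point. The design effects borrowed below do reproduce: 1 + 149 × 0.005 = 1.745 and 1 + 149 × 0.025 = 4.725.

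**Inputs from the article.** 24 clusters of 150 per arm, so 3,600 women; infant mortality 111 per 1,000 live births in Siaya; detectable differences of 3.5 to 7.5 percentage points (Sample size); skilled delivery 69.6%.

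**Assumptions, not in the article.** Stillbirths 15 to 35 per 1,000 births; early deaths 10 to 30 per 1,000 live births; shifts of 3 to 10 per 1,000 births; the attendance ICCs applied to deaths.

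**1. A true excess of stillbirths.** Extra losses = 3,600 × stillbirth risk × (relative rise − 1).
- Lowest: 3,600 × 0.015 × 0.25 = 13.5.
- Highest: 3,600 × 0.035 × 0.5 = 63.
- Middle: 3,600 × 0.025 × 0.25 = 22.5. Infant mortality stays at 111 per 1,000. The count of infant deaths falls slightly, from 389.6 to 387.1, because there are fewer live births.
- Per 1,000 pregnancies, the middle case takes stillbirth plus infant death from 25 + 0.111 × 975 = 133.2 to 31.25 + 0.111 × 968.75 = 138.8. The combined count shows what the current measure cannot.

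**2. How visible a stillbirth row would be.** SE of the arm difference = √(2p(1−p)/3,600 × DE). At p = 0.025 this is 4.86 per 1,000 (DE 1.745) or 8.00 per 1,000 (DE 4.725). A relative rise of 1.25 is 6.25 per 1,000, or 1.3 or 0.8 SE. A rise of 1.5 is 12.5 per 1,000, or 2.6 or 1.6 SE. The row would inform judgement and would not by itself settle the matter. These figures use full enrolment, so an early look would be weaker.

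**3. A pure shift from stillbirth to early death.** Move s births per 1,000. Infant mortality becomes (d + s)/(LB + s), where d is infant deaths and LB live births; total loss is unchanged.
- At 111 per 1,000, 25 stillbirths and s = 5: (108.2 + 5)/(975 + 5) = 115.5 per 1,000, a risk ratio of 1.04. Total loss is 133.2 before and after. Across s = 3 to 10 the ratio is 1.02 to 1.08.
- At an early look with 20 early deaths per 1,000 and s = 5: (19.5 + 5)/980 = 25.0 per 1,000, a ratio of 1.25. Across 10 to 30 early deaths per 1,000, s = 5 gives 1.16 to 1.51.
- In SE units, s = 5 is about 0.5 or 0.3 SE at 111 per 1,000, and about 1.1 or 0.7 SE at 20 per 1,000 (lower and higher ICC).

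**4. Is s = 5 plausible?** The mechanism can act only on births moved from home to facility. If 3.5 to 7.5 points of births move, at a 2.5% stillbirth risk, they contain 0.035 × 25 = 0.9 to 0.075 × 25 = 1.9 stillbirths per 1,000 births. On an assumed early death risk of 15 per 1,000:
- all of them converted: (15 + 0.875)/15 = 1.06 to (15 + 1.875)/15 = 1.13;
- 10 to 20% converted: at most (15 + 0.375)/15, so about 1.01 to 1.03.

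**The case against.** The strongest defence is that the section gives no denominator, window or boundary for infant mortality. The committee works under a charter, and a detailed analysis plan is to be finalised with it, so report rows may be set there. Birth outcome is collected, and the committee may ask for it at any meeting; the primary outcomes are an example of what it may request, not a limit. Its advice is a judgement, with no numerical boundary for a ratio to trip.

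Much of this stands. A reader might infer that pregnancy losses go unmonitored. The documents do not support that: live birth with 48 h survival is a named outcome with planned sources, and the committee can request it. The per-live-birth reading rests on ordinary usage and the Study setting section, not on a definition in the interim section.

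A reader might also infer that better facility coverage would look like harm. Applying 10 to 20% conversion to every stillbirth in the cash arm, at 2.5% stillbirth and 1.5% early death, gives (15 + 2.5)/15 = 1.17 to (15 + 5)/15 = 1.33. That needs 2.5 to 5 converted stillbirths per 1,000 births, against the 0.9 to 1.9 available among moved births. Even moving all of the 30.4% of births without a skilled attendant would supply only 0.304 × 25 = 7.6 per 1,000, of which one third to two thirds would have to convert. The documents do not say that facility delivery causes such a shift.

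What the defence does not answer is that the article itself fixes the content of the standing report. A committee shown level infant mortality has no prompt to ask about stillbirths, and the one example of a further analysis, the primary outcomes, includes no birth outcome.

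**Conclusion.** The point holds as a gap in the routine by-arm report. As named, the two safety measures would not show an excess of stillbirths: on the assumed rates, about 14 to 63 extra losses among 3,600 women with infant mortality unchanged. This rests on the ordinary meaning of infant mortality and on assumed stillbirth risks.

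The shift effect is real in direction but secondary. It is 1.02 to 1.08 at the article's own infant mortality. At an early look it is about 1.01 to 1.03 with plausible conversion, and at most 1.06 to 1.13 given the number of births likely to move. It would seldom look conclusive. No calculation or analysis in the protocol is broken. This is a cheap improvement to safety monitoring.

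**What to change.** In the interim analysis section, extend the report by arm to:

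- stillbirth;
- stillbirth or child death within 48 h, per enrolled pregnancy with a known or due birth outcome, with the number of outcomes still unknown;
- infant mortality, defined per live birth;
- maternal mortality.

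Use the clinic records and survey-two delivery outcomes already planned for the secondary outcome. These are meant to cover facility and home births alike, whereas the survey source for later child deaths reaches half of the participants.

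Leave miscarriage out of the composite. It is not a listed data item, and women paid to attend may have more losses recorded. If it is shown, give it a separate row with a note on differential ascertainment.

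The cost is a few table rows and having birth outcomes ready for each report. Manual record extraction is planned to start only at the end of enrolment, so completeness for the 2018 look needs attention. Protocol version 2.1 is dated 26 December 2018, so the change could still be made for the 2019 look.

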#### Final analysis

Final analyses will be by intention-to-treat, based on all enrolled mothers who were pregnant during the recruitment period (July 2017 to July 2018) and their children, regardless of whether they received the intervention or not. We will test for differences in the primary outcomes between the intervention and control arms using logistic regression for binary outcomes, and ordinal logistic regression for ordinal outcomes, adjusting for clustering using random effect models.

Provided there is no qualitative difference between the odds ratios for the effect of the intervention across the primary outcomes, then only the summary odds ratio will also be presented. This will be the primary effect measure for the trial. It will be estimated using independence estimating equations because not all participants will be eligible for all outcomes (e.g. vaccination of infants who died) and this approach avoids any implicit imputation of outcomes for ineligible participants.

Besides the issue of ineligible outcomes described previously, there should be no completely missing data on the primary outcomes. If a record of attendance cannot be found in the patient records in the study area, this will be interpreted as failure to attend. However, participants may make visits to facilities outside the study area, often in relation to temporarily or permanently moving to reside outside the study area. As described in Section Collecting data on visits to facilities outside the study area, data on visits outside the study area will be available for all higher-risk participants, and dependent on telephone interviews also available (though approximate) for up to half the lower-risk participants.

We plan to conduct our primary analysis based only on data on lower-risk participants from visits within the study area if it seems this will not lead to bias, but to use the approximate number of visits outside the study area from (up to) half the lower-risk participants to impute these additional visit data for the remaining participants if it seems bias will otherwise arise. We prefer not to impute visits out of the study area unless this is required because the data on visits outside the area by lower-risk participants are only approximate.

The precise criteria by which will we judge if bias is likely, and exactly how imputation will be conducted if necessary, will be specified in our analysis plan. If imputation is conducted then the analysis based on imputed data will be considered primary.

In our primary analysis we will adjust for key predictors of the primary outcomes, and any other baseline factors of clusters or individual participants for which an important imbalance is seen between arms. We will also carry out sub-group analyses to examine whether the effect of the intervention differs by wealth/multi-dimensional poverty quintile to understand the equity impact of the intervention.

The final analysis will be presented according to the consolidated standards of reporting trials (CONSORT) requirements for cRCTs [45, 46]. Both the interim and final analyses will be conducted by the trial statisticians. A detailed statistical analysis plan will be prepared and finalized in consultation with the Trial Steering Committee (TSC)/DMC before analysis begins.

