**Fig. 1 Fig1:**
[figure not shown]
Schedule of enrolment, interventions and assessments. *MNCH appointments/visits – Standard maternal and child health visits described in Additional file 1. **Covariates - see Table 1. ***Health outcomes - see Additional file 2. MNCH, maternal, newborn and child health; ANC, antenatal care; PNC, postnatal care

Once enrolled into the study, the participant is followed 341 up until the expected baby is 1 year of age (Additional file 1). Participants who move out of the study location are considered lost to follow up.

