### Intervention strategy

#### Cash transfer value

The intervention is a conditional cash transfer (CCT) payment for each facility appointment attended for ANC, delivery, postnatal care and childhood immunization; and referrals related to any of these visits. For each verified health visit that is made on time following enrolment, a woman receives a cash transfer of Ksh 450 (4.5 USD). The value reduces by one quarter for each week of delayed visit, and no reward is offered for any visit made 3 weeks after the appointment date. On average, Ksh 450 equates to the transportation cost of a local taxi to the health facility, and is a value that has been approved by the research ethics committee for many studies in the region as reasonable compensation for research participants.

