##### Card reader

Card readers are installed in all participating intervention and control facilities. The device used is a Famoco Fx100, an android near field communication (NFC) card reader. The Fx100 has an in-built SIM card slot and is enabled for GSM/GPRS/3G communication. The card reader is connected to a remote server that electronically personalizes the NFC card of the user during enrolment, and tracks her subsequent health visits. Each time the *Afya* card makes contact with the reader, the information stored on the card is transmitted to the reader and from the reader to the card, then subsequently from the reader to the web portal (an electronic database) [29]. The card also has an offline transacting capability with the terminal reader that enables it to function during occasional absence of connectivity. The reader also comes with a power back up that enables it to function when there is no electricity for a prolonged duration.

This web portal enables the study team to remotely track participants’ health facility attendance throughout pregnancy and up until 12 months after delivery, and to effect the cash transfer payments. On confirmation of a timely visit, payments to participants are made directly from the project’s bank account where the funds are held, to the participants’ mobile money accounts. This is achieved through integration of the Famaco FX card reader system with Safaricom Bulk Disbursement Service, the leading mobile money payment provider in Kenya. A payout is thus automatically triggered following the touching of the *Afya* card on any of the 48 terminal readers. Manual payouts are triggered by the project team upon verification of visits by participants who forget to carry their clinic books during the visits or who visit non-enrolling facilities that have no readers installed. Pregnant women are therefore not restricted to using the facility at which they were enrolled as long as it is within the study evaluation zone, which is Siaya County. Health visits outside Siaya County are not recorded or rewarded, except for high-risk groups (see Collecting data on visits to facilities outside the study area).

The web portal is continually monitored by a member of the project team to ensure that there are no pending payments for timely health visits attended. The project team also makes regular visits to the health facilities to monitor whether all system components function as expected, and to resolve any challenges promptly.

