#### Gratuity for control group participants

Although the primary function of the cash transfer is to motivate health facility visits, the cash payment could additionally motivate women in the intervention group to carry their ANC clinic books when they visit the clinics. This is because the *Afya* card embedded in the book facilitates automated payment transfers to the women at the end of the clinic visit. Forgetting to carry the ANC clinic card during ANC visits delays the payment as the visit must be verified manually. Therefore, to balance out the possible health effects of carrying the ANC clinic book in the intervention and control groups, a nominal gratuity for carrying the clinic book is offered to women in the control group, who might have lower motivation to carry the book. The gratuity is in the form of mobile phone airtime with a value of Ksh 50 (0.5 USD) for every eligible visit, transferred through the same system that is used to issue the incentives. Ksh.50 is approximately equivalent to the cost of five bananas purchased at a market and would not compensate participants for the cost of attending the health visit. It may however, be an incentive for a woman who was going to go to the clinic anyway, to carry her clinic book.

Participants in both study groups are followed up in the same way, including monitoring of visits using the electronic-based system and telephone surveys conducted at key points in the care continuum. Follow up is described Data collection methods.

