#### Manual extraction of health records

At the end of the enrolment period and throughout the remaining trial period, health seeking and health status data will be manually extracted from routine health records held at facilities. Additional file 2 shows the detailed health records that are taken during ANC, delivery and postnatal health visits. A record book is also available at health facilities for each child, and a child growth card is issued to women who deliver at health facilities. This card contains key data on the newborn from birth until they reach 5 years of age.

Towards the end of the trial period, data on health visits and services will also be collected from referral facilities attended by the participants. Data on visits made to health facilities outside Siaya County will not be extracted or rewarded. Participants will be identified in the records by their study ID number^1^ to ensure participant confidentiality.

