#### Collecting data on visits to facilities outside the study area

The strategies used to collect these data vary according to whether or not the participant is considered high risk. High-risk groups in this study comprise mothers whose ANC records show HIV-positive status, positive malaria smear test and/or other diagnoses of sexually transmitted infection (STI). These diagnoses are likely to require referrals and additional health visits not captured in routine ANC or PNC records. Furthermore, participants with these complications are more likely to be lost to the routine monitoring systems as they might completely shift their ANC, delivery and PNC visits to the referral centers that handle these infections.

We will track all health visits made by high-risk participants only, including those taking place in neighbouring counties outside the evaluation zone. This would be done through extra phone calls to the participants to elicit information on health facilities visited. The study team will then visit those facilities and manually extract health records as described previously. The exception to this case would be if care is sought outside the Western Kenya region, in which case the data will be considered missing in the case of a single instance of care seeking, or the participant will be classed as lost to follow up if they have permanently transferred.

For lower risk participants, we shall incorporate questions relating to the primary outcomes (facility visits, child vaccinations etc.) into the telephone surveys (see Telephone surveys) administered to 50% of participants. This gives participants the opportunity to report visits both outside the study area and within, and we shall also ask whether the participant moved temporarily or permanently outside the study area. By comparing these self-reports with the data on visits within the study area (collected by other means) we will be able to approximately deduce the number of visits made outside the study area. These additional visits will not be verified by the study team as will be done for high-risk participants.

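### Scoring care with no in-county record as non-attendance exposes the primary outcomes to misclassification that can depend on arm

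*Protocol article*

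**What the plan says.** **Scoring.** Final analysis sets the default: "If a record of attendance cannot be found in the patient records in the study area, this will be interpreted as failure to attend". The same section accepts that women may use facilities elsewhere, often because they have moved, and expects no completely missing primary-outcome data.

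**Payment and capture.** Card reader: "Health visits outside Siaya County are not recorded or rewarded, except for high-risk groups". The intervention arm receives Ksh 450 for an on-time visit (Cash transfer value). The control arm receives "mobile phone airtime with a value of Ksh 50 (0.5 USD) for every eligible visit".

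**Who is traced.** Under Collecting data on visits to facilities outside the study area, "High-risk groups in this study comprise mothers whose ANC records show HIV-positive status, positive malaria smear test" or another STI diagnosis. No time limit is put on when the diagnosis is made. All visits by these women are followed, including those in neighbouring counties, and checked against facility records. Lower-risk women are only asked, in the 50% telephone sample, and their answers are not verified.

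**Safeguard.** Out-of-area visits will be imputed for the remaining lower-risk women if bias seems likely, and the imputed analysis then becomes primary. The criteria are left to the analysis plan. The stated preference is not to impute.

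**Survey 2.** By its heading it goes to women with no facility delivery; by its text, to mothers who gave birth at home. The interviewer is blinded. "This survey collects information on delivery date, delivery outcome, who conducted the delivery", among other items. Table 1 does not name it as a source for facility delivery; the telephone data listed there cover high-risk women and half of the others.

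**Movers and out-of-county records.** Below Fig. 1: "Participants who move out of the study location are considered lost to follow up". Manual extraction of health records: "Data on visits made to health facilities outside Siaya County will not be extracted or rewarded", with no exception for high-risk women.

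**The concern.** For lower-risk women the payment boundary and the counting boundary are the same line. A woman in the cash arm who would have delivered in a neighbouring county has a reason to deliver in Siaya instead. Her care is no greater, but she changes from a non-attender to an attender. A control woman has a much weaker reason to switch, so the classification error can differ between arms on the primary outcomes.

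A second route runs through the high-risk label. A diagnosis at the enrolment visit cannot depend on later attendance, but one found at a later visit can, and the intervention aims to increase later visits. A woman newly labelled high-risk then has her out-of-county visits traced and counted.

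The passages on movers and on out-of-county records also give different answers for the same woman.

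**Working it through.** **1. The plan's own figures (Sample size).** Inputs: 24 clusters per arm of 150, so 3600 women; ICC 0.005 or 0.025; 5% significance, taken as two-sided.
- Design effect = 1 + 149 × ICC = 1.745 and 4.725.
- Effective size per arm = 3600/1.745 = 2063 and 3600/4.725 = 762. Both agree with the protocol.
- Differences detectable with 80% power from 50%: 4.36 and 7.15 points; from 80%: 3.37 and 5.42 points. The stated 4.5, 7.5, 3.5 and 5.5 are these rounded up to the next half point.
- Near 70% the detectable difference is 3.9 points (ICC 0.005) or 6.4 points (ICC 0.025).

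**2. Model with no true effect.** True attendance p = 0.70 in both arms. As a proxy, Study setting gives 69.6% skilled attendance at delivery. The other inputs are assumptions, because the documents give none of them: s, the share of attended care that is out of county; r, the share of that care that cash moves into the county; h, the share of women labelled high-risk, equal in both arms, whose out-of-county care is captured.
- Recorded control rate = p[1 − s(1 − h)]
- Recorded cash rate = p[1 − s(1 − r)(1 − h)]
- Spurious difference = p·s·r·(1 − h)

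The last column is the chance of a significant result favouring cash (nominal 2.5%), by normal approximation on the effective sizes.

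| s | r | h | Control | Cash | Difference (points) | OR | False positive, ICC 0.005 / 0.025 |
|---|---|---|---|---|---|---|---|
| 5% or 10% | 0 | 0 | 66.5% or 63.0% | same | 0 | 1.00 | 2.5% / 2.5% |
| 5% | 50% | 0 | 66.5% | 68.25% | 1.75 | 1.08 | 22% / 11% |
| 10% | 50% | 0 | 63.0% | 66.5% | 3.5 | 1.17 | 65% / 30% |
| 10% | 50% | 30% | 65.1% | 67.55% | 2.45 | 1.12 | 38% / 17% |

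**3. Label route alone.** Difference = p·s·(h in cash arm − h in control). With an assumed 40% against 30%, this is 0.70 × 0.05 × 0.10 = 0.35 points at s = 5% and 0.7 points at s = 10%.

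**4. True effect, no care moved, labels balanced.** Take 70% against 75%, true OR (0.75/0.25)/(0.70/0.30) = 1.29. With s = 10% and nothing captured, the recorded rates are 63.0% and 67.5%, OR (0.675/0.325)/(0.63/0.37) = 1.22. The rule then works against the intervention.

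**5. Passages side by side.** A lower-risk woman who leaves the area is lost to follow-up in the text below Fig. 1, but a non-attender under Final analysis. A high-risk woman's care outside Western Kenya is missing, or she is lost to follow-up if she has transferred permanently (Collecting data on visits to facilities outside the study area), while Final analysis expects nothing completely missing. Out-of-county records are not extracted according to Manual extraction of health records, but are extracted for high-risk women elsewhere. Card reader excepts high-risk groups from the bar on rewards; Manual extraction of health records does not.

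**The case against.** The protocol does not treat the no-record rule as final. The next sentences acknowledge out-of-area visits, provide for imputation, and make the imputed analysis primary if it is done. That the criteria wait for the analysis plan is proper and is no fault here. This stands, and it rules out any statement that the primary outcomes simply are biased. What remains is what the protocol itself fixes: a non-imputed default, and a fallback built on approximate, unverified answers from at most half of lower-risk women. Survey 3, one source of those answers, is not blinded.

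Direction is also open. Enrolment requires six months' residence in the catchment, and out-of-area care is often put down to moving home, which a small payment may not change. With r = 0 and balanced labels there is no spurious difference, only attenuation.

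A reader might also infer that cash is paid only for in-county care, or that facility delivery is the outcome worst affected. The first overlooks the exception in Card reader. The second is not shown: survey 2 could find many out-of-county births in both arms, blinded, if it were used. But survey 2 has limits of its own. Its text is narrower than its heading, and it lists the attendant, not the place of birth.

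The missing exception under Manual extraction of health records may be no more than a general rule stated without its qualification. It still needs the qualification.

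**Conclusion.** The concern holds as a risk of arm-dependent misclassification that can favour the cash arm, and it deserves correction before analysis. The stronger reading, an established bias towards cash, is not supported: the documents give neither the out-of-county share nor any evidence that cash moves care across the border, and they provide for conditional imputation.

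Under the stated assumptions (70% true facility delivery, 5-10% of attended care out of county, half moved in), the spurious gain is 1.75-3.5 points with nothing captured. At the 10% share it is about 2.5 points with 30% of women high-risk and captured, and it is 0 if nothing moves. The upper figure is close to the 3.9 points detectable at the low ICC, but well short of the 6.4 points at the moderate ICC. The label route adds less than about 1 point at these shares. The contradictions over movers and out-of-county records need no assumptions.

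**What to change.** 1. **Facility delivery.** For women with no in-county delivery record, use blinded survey 2 as a source for this outcome and list it there in Table 1. Send it to all women without a recorded facility delivery, as its heading says, and confirm that it asks where the birth took place. Treat non-responders as missing, with best-case and worst-case sensitivity analyses.
2. **High-risk label.** Set it from the ANC record of the enrolment visit, so that later attendance cannot change whose out-of-county visits are traced. Keep the verified visits of high-risk women in the primary analysis. Removing them to treat both risk groups alike would apply the no-record rule to everyone and, in the model above, widen the 10% case from 2.45 to 3.5 points.
3. **Reconcile the text.** Give one rule for movers and for missing care across the text below Fig. 1, Collecting data on visits to facilities outside the study area, and Final analysis. Carry the high-risk exception into Manual extraction of health records, so that it agrees with Card reader on both extraction and reward.

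**Cost.** Mostly wording, plus any survey 2 calls or a place-of-birth question not already included. The downside is reliance on self-report for births without a record. Recruitment closed on 31 July 2018, so many of these calls may already have been made. If place was not asked, the attendant is only a proxy for it and should be reported as such.
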